## Abstract

**Background:**

There is a crisis of non-communicable diseases (NCDs) in the Pacific Islands, and poor diets are a major contributor. The COVID-19 pandemic and resulting economic crisis will likely further exacerbate the burden on food systems. Pacific Island leaders have adopted a range of food policies and regulations to improve diets. This includes taxes and regulations on compositional standards for salt and sugar in foods or school food policies. Despite increasing evidence for the effectiveness of such policies globally, there is a lack of local context-specific evidence about how to implement them effectively in the Pacific.

**Methods:**

Our 5-year collaborative project will test the feasibility and effectiveness of policy interventions to reduce salt and sugar consumption in Fiji and Samoa, and examine factors that support sustained implementation. We will engage government agencies and civil society in Fiji and Samoa, to support the design, implementation and monitoring of evidence-informed interventions. Specific objectives are to: (1) conduct policy landscape analysis to understand potential opportunities and challenges to strengthen policies for prevention of diet-related NCDs in Fiji and Samoa; (2) conduct repeat cross sectional surveys to measure dietary intake, food sources and diet-related biomarkers; (3) use Systems Thinking in Community Knowledge Exchange (STICKE) to strengthen implementation of policies to reduce salt and sugar consumption; (4) evaluate the impact, process and cost effectiveness of implementing these policies. Quantitative and qualitative data on outcomes and process will be analysed to assess impact and support scale-up of future interventions.

**Discussion:**

The project will provide new evidence to support policy making, as well as developing a low-cost, high-tech, sustainable, scalable system for monitoring food consumption, the food supply and health-related outcomes.

## Introduction

Non-communicable diseases (NCDs), including cardiovascular diseases, diabetes, cancer, and chronic respiratory diseases, are the leading causes of death in the world, killing more people each year than all other causes combined. NCDs also represent the single largest cause of premature mortality in the Pacific Islands [1]. For small Pacific economies, increasingly impacted by climate change and more recently by the COVID-19 pandemic [2, 3], prevention is a must because the increasing cost of treating NCDs is overwhelming [4]. Pacific leaders recognize this, as demonstrated by the plethora of policies, backed by ministerial and bilateral support. This includes the Pacific Monitoring Alliance for NCD Action (MANA) supported by the World Health Organization, the Pacific Community, Pacific Research Centre for the Prevention of Obesity and Non-Communicable Diseases and the Pacific Island Health Officers’ Association [5], whilst in Tonga funds from taxes are being strategically directed to health promotion through Tonga Health [6].

World Health Organization (WHO) country disease profiles show an increasing prevalence of NCD risk factors, such as hypertension and diabetes, in the Pacific [7, 8]. For example, in Fiji, 34% of deaths are from cardiovascular diseases and 22% from diabetes, and 25% of males and 30% of females live with obesity [7]. Poor diets are a major contributor to these deaths. Around one third of the increase in blood pressure over the last two decades, in Samoa, can be explained by rising obesity levels [9] which in turn can be explained by changes in food availability [10]. An underlying driver of these high rates of diet-related diseases is the transition from diets based on locally-grown foods [11, 12] to diets characterized by imported foods, refined oils, sugar, confectionery, and processed meats [13, 14], resulting in high population intakes of salt and sugar.

Evidence that food policy interventions improve diets is increasing. Systematic reviews show that taxes and subsidies create a consistent positive effect on consumption across a range of taxation levels [15]. Modelling studies have demonstrated that fiscal interventions can reduce cardiovascular risk and diabetes incidence, and are largely cost effective [16–18]. Interventions that promote reformulation of processed food to reduce salt and sugar content have also been shown to reduce cardiovascular disease risk [19, 20]. A recent systematic review of school food environment policies demonstrated a positive impact on dietary behaviours whilst highlighting the need for longer term investigations assessing the impact of these policies on children’s metabolic risk [21].

Globally, the World Health Organization (WHO) has established maximum recommended intake levels for salt and sugar consumption [22, 23], and WHO recommends that countries introduce policies to reduce population intake of salt and both free and added sugars through its Global NCD Action Plan [24]. In line with global recommendations, the Government of Fiji implemented a tax on sugar sweetened beverages (SSBs), reduced taxes on imported fruit and vegetables, and adopted a cross-ministerial school food and nutrition policy. Also, the Government of Samoa agreed new food regulations, including taxes for salt and sugar [25] increased taxes on SSBs [26] and has introduced national School Nutrition Standards (2012).

While both countries have established a range of policies, effective implementation is a challenge [27]. For example, compliance to nutrition standards in educational institutions has hovered around 30–40% in Samoa, despite significant efforts by the Ministry of Health to revise, promote, and monitor them [28]. Similarly, in Fiji, a Technical Advisory Group was set up to establish policies to reduce salt, fat and sugar consumption, but there was no clear process for implementation [29].

Significant barriers potentially stand in the way of effective implementation of these policies [13, 30]. These include inappropriate criteria for setting levels for taxes or reformulation, or lack of established processes for implementation and monitoring/enforcement. There is also very little national context-specific evidence on the effectiveness or cost effectiveness of food policy interventions in Pacific Island countries [31, 32].

To help Pacific countries counter this, we have designed a five-year project that will take a comprehensive, empirical approach to understand and strengthen the policy making processes. The emphasis will be engaging communities and policy makers and implementing, at scale, the best policies to reduce diet-related diseases, particularly hypertension and diabetes in Fiji and Samoa.

## Methods

The overall aim is to test the feasibility and effectiveness, of policy interventions to reduce salt and sugar consumption in Fiji and Samoa, as well as factors that will support sustained implementation of the interventions. We will do this through use of a pragmatic Type 3 implementation effectiveness hybrid trial (See Fig. 1) [33]. We will use an iterative adaptive process to strengthen and monitor food policy interventions, including (1) a policy landscape analysis to map existing policy content, stakeholders and politics; (2) repeated cross sectional surveys to measure dietary intake, food sources and diet-related biomarkers, and implementation of school food policies; (3) Systems Thinking in Community Knowledge Exchange (STICKE) to engage stakeholders to identify, implement and monitor actions to strengthen food policy interventions; (4) evaluation of impact, process and cost-effectiveness of interventions.

**Fig. 1 Fig1:**
[figure not shown]
Study design based on type 3 effectiveness-implementation hybrid trial

The interventions will be staggered so that one country can provide comparison data during the first year, and we will use publicly available data (e.g. WHO Stepwise risk factor (STEPS) survey and the Household Income Expenditure Survey (HIES), as well as data from other national cross-sectional surveys, to understand policy impact.

Main outcome measures: changes in population intake levels of salt and sugar, salt and sugar levels in foods, and food prices (measured through surveys done at baseline and follow-up). Changes in blood glucose and blood pressure and overweight/obesity (measured in consecutive STEPS surveys).

Main process measures: reach, adoption, implementation (context, costs and adaptations made during delivery) of the implemented food policies.

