#### 24-h diet surveys

The objective of the 24-h diet recall surveys is to provide an in-depth robust assessment of what adults are eating, including the contributions of different foods to salt and sugar in the diet. 24 h diet recall surveys can be used to accurately assess changes in population intake of nutrients [47]. Urinary analysis is the best way of estimating sodium intake. However, both Fiji and Samoa monitored sodium intake using urinary analysis in 2013 and 2016 [48, 49] and it is not expected to have changed since then. Additionally, spot urine samples will be collected as part of the next WHO STEPS surveys in each country (planned for 2021), so it is not necessary to include urinary sodium analyses as part of this project. In contrast, whilst Fiji has a National Diet and Nutrition Survey (NDNS) from 2015, this will not be repeated until 2025. We will, therefore, undertake dietary surveys in years 1 and 4 in Fiji and 2 and 5 in Samoa.

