##### Data collection process

Research assistants will be trained in the 24-h diet recall survey data collection procedures. The entire enrolment and data collection process will be done face-to-face in English (which is spoken by more than 90% of the populations in these countries) by trained research assistants. Research assistants will be able to assist participants by orally translating written material into the local language. Participant information sheets and consent forms will be available in Hindi and Fijian (for Fiji). Each consented participant will then be assigned a unique ID number. Participants will then be interviewed by the research assistant to:i.Complete a general questionnaire on basic demographics, disease history and medication useii.Complete the 24-h diet recall survey (see below for more details)iii.Record height, weight, waist circumference and blood pressure [53]

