### Systems thinking in community knowledge exchange (STICKE)

Building on the previous work done in Fiji [58], and informed by baseline outcome data and the policy landscape analysis, we will invite key government, industry and civil society leaders to participate in a structured, facilitated process [59] to build consensus on population level actions to reduce sugar and salt. We will engage 15–20 participants in each country, recruited through known contacts of the existing project team, in a series of deliberative consensus building forums. The objectives will be to understand diets and the drivers of poor diet, map existing interventions, and then discuss barriers and opportunities to strengthening policy implementation.

We will use techniques adapted from community based participatory system dynamics, notably group model-building and software (STICKE), to engage stakeholders in building a causal loop diagram reflecting the complexity of the drivers of unhealthy food availability and consumption and identify new or adapting existing interventions to reduce salt and sugar. Specific food policy interventions identified through a preliminary stakeholder meeting in January 2020 include:Taxes on foods or drinks high in salt or sugar – we will identify steps that need to be taken to strengthen existing implementation, including amending the level or type of taxation or extending to other foods.Programs to influence the nutrient content of available processed foods - we will identify new policies or opportunities to strengthen implementation of existing policies including engaging industry on reformulation or by working with importing agencies to change the balance of imports (i.e. having nutrient content restrictions to specify which foods that can be imported).School food policies and programs - we will review existing programs and identify opportunities to strengthen implementation and broaden reach including through training and capacity building and the strengthening of monitoring and accountability mechanisms.

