### Evaluation of impact, process and cost effectiveness

#### Impact evaluation

Depending on the interventions implemented in each country, overall evaluation of impact will examine the extent to which the intervention has had an effect in terms of dietary intake, changes in knowledge, attitudes and behaviours relating to food or the food supply, using the baseline and monitoring surveys in each country. Where school food interventions have been supported as part of the project, additional outcomes, in terms of numbers of schools implementing the interventions, will also be measured. Changes in blood pressure or blood glucose since implementation of the interventions will be extracted from other surveys conducted in Fiji and Samoa throughout the project and the extent to which these are likely to be due to the intervention will be assessed through the process evaluation.

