### Strengths and limitations

The strength of this project is that it explores the challenges of implementing food policies in real world settings, with parallel interventions in Fiji and Samoa allowing for shared learning and comparative analyses. The in-depth policy landscape analysis and systems thinking approach to engaging the community and policy makers will hugely increase the chances of culturally appropriate policies being adopted and implemented effectively. The adaptive nature of the methodology means that it is ideally suited to responding to contextual changes affecting implementation, including the additional food security challenges posed by the unfolding COVID-19 situation. Whilst some of the policy analysis is already underway, and staff are being recruited to work with in-country project leads at Fiji National University, it will not be possible to commence the community dietary surveys, which rely on community health workers and include collection of blood samples, until social distancing measures in Fiji have been eased. However, planning, protocol development and training are underway, and with the COVID-19 situation currently seeming relatively stable in Fiji and Australia, we expect that the project should be able to progress with minimum delay.

A further limitation is that, based on practicality and limited resources, the community surveys will be limited to the main island in each country and we will not be able to measure impact in outer islands. However, we expect the research to benefit residents of outer islands because the strategies we co-design with policy makers are targeted at the national level.

Whilst the interventions are context specific, we predict that the evidence generated on strengthening implementation could be used to inform future policy interventions, not only in Fiji and Samoa, but also in Australia and potentially in other small island states. The main limitation is that it is not possible to do a randomised controlled trial and that the interventions are context-specific so the intervention effectiveness findings may not be generalisable to other countries or regions. However, it is likely that the lessons learned can be used to strengthen implementation and monitoring of polices in other countries. In addition, the processes for engaging policy makers and the innovative methods for monitoring may be replicated elsewhere.

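### No post-implementation STEPS round is named for the blood pressure, glucose and obesity outcomes, and the project's own before-and-after blood pressure and weight data are given no outcome role

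*Protocol article*

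**What the plan says.** All references are to the protocol article.

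- **Methods, main outcome measures (below Fig. 1).** Intake, food composition and prices come from the project's baseline and follow-up surveys. The health outcomes have a different source: "Changes in blood glucose and blood pressure and overweight/obesity (measured in consecutive STEPS surveys"). The preceding paragraph also allows public data, including other national cross-sectional surveys, to be used to understand policy impact.
- **Impact evaluation.** The source is surveys run by others over the project's lifetime: "Changes in blood pressure or blood glucose since implementation of the interventions will be extracted from other surveys conducted in Fiji and Samoa throughout the" (sentence cut here). Whether such changes can be attributed to the interventions is left to the process evaluation. Overweight and obesity are not mentioned here, so their source rests on the main outcome paragraph alone.
- **24-h diet surveys.** The one STEPS date appears in the explanation of why urine will not be collected: "spot urine samples will be collected as part of the next WHO STEPS surveys in each country (planned for 2021"). The same section says the project will "undertake dietary surveys in years 1 and 4 in Fiji and 2 and 5 in Samoa".
- **Data collection process.** Interviewers will "Record height, weight, waist circumference and blood pressure". No blood measure is listed.
- **Survey procedures.** Sodium and sugar intake are the primary outcomes, and their dietary sources are key secondary outcomes. Blood pressure and anthropometry are not mentioned.
- **Strengths and limitations.** The dietary surveys had not started, and are said to "include collection of blood samples". The abstract and the opening of Methods likewise say the repeat surveys measure diet-related biomarkers.

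**The concern.** An impact outcome needs one measurement before the interventions can act and one after. For the three health outcomes the article names a source that it does not control. The only date it gives for that source falls near the start of the project. The second half of the before-and-after pair is therefore not secured on paper.

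The project meanwhile plans two waves of its own that fall on either side of the intervention period and record blood pressure and body size. The article does not say these will be analysed for change. It applied the timing check elsewhere: because Fiji's national diet survey will not be repeated until 2025, the project runs its own dietary survey. The same reasoning was not carried over to blood pressure and weight.

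At stake is whether outcomes tied to the project's target diseases, hypertension and diabetes, will have any estimate over the right interval. For glucose the question is harder, because the article is inconsistent about whether the project draws blood.

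**Working it through.** **1. Timeline**

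Inputs: "we have designed a five-year project" (Introduction); surveys in years 1 and 4 (Fiji) and 2 and 5 (Samoa); STEPS in 2021. Year 1 has no calendar date. The anchors are that candidate interventions were "identified through a preliminary stakeholder meeting in January 2020" (STICKE section) and that the dietary surveys had not begun at the time of writing. I take year 1 as 2020 or 2021. Calendar year = year 1 + project year − 1.

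| Year 1 (assumed) | Country | Baseline | Follow-up | 2021 minus baseline | Follow-up minus 2021 |
|---|---|---|---|---|---|
| 2020 | Fiji | 2020 | 2023 | 1 | 2 |
| 2020 | Samoa | 2021 | 2024 | 0 | 3 |
| 2021 | Fiji | 2021 | 2024 | 0 | 3 |
| 2021 | Samoa | 2022 | 2025 | −1 | 4 |

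In every row the 2021 round is within one year of baseline and two to four years before follow-up. The STICKE section says intervention selection is informed by baseline data and by the policy landscape analysis, so the interventions come after baseline. A pair made of an earlier STEPS round and 2021 would then cover a largely pre-intervention period. A pair made of 2021 and a later round would cover the right period, but the article names no later round.

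**2. Survey size used for the precision check**

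The sample size section gives 300 per country per time-point, power 0.9 and a design effect of 1.5. To confirm that 300 is the working figure, take salt (SD 3.6, difference 1.2) with two-sided alpha 0.05, which the article does not state:

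- n per time-point = 2 × (1.960 + 1.282)² × (3.6/1.2)² = 189.1, so 190 (191 by t-test)
- times 1.5 = 285 to 287, consistent with rounding up to 300
- 300 / 0.5 response = 600 approached, as stated

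Free sugar (SD 5.4, difference 1.8) has the same ratio and gives the same answer. The Sampling section says 3600 adults. The calculation and the 600 to be approached support 300, so I use 300.

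**3. Precision for systolic blood pressure from the project's own waves**

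The article gives no blood pressure SD. I assume 15 to 22 mmHg.

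- Effective n per wave = 300 / 1.5 = 200
- SE of change = SD × √(2/200) = 0.1 × SD
- Detectable change at 0.9 power = (1.960 + 1.282) × SE
- 95% confidence interval half-width = 1.960 × SE

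| Assumed SD (mmHg) | SE | Detectable change, 0.9 power | 95% CI half-width |
|---|---|---|---|
| 15 | 1.5 | 4.9 | 2.9 |
| 18 | 1.8 | 5.8 | 3.5 |
| 20 | 2.0 | 6.5 | 3.9 |
| 22 | 2.2 | 7.1 | 4.3 |

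**4. Blood samples**

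The limitations section says the dietary surveys involve blood samples. The itemised list under Data collection process has a questionnaire, the diet recall, body measurements and blood pressure, and no blood. Both statements describe the same surveys and they do not agree. Which is correct decides whether the project has a glucose source of its own.

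**The case against.** The strongest case is that the problem is inferred from silence. STEPS is an external survey programme. The article dates one round only to explain why it will not collect urine, and does not offer that as a list of rounds for the outcome analysis. The impact section asks for change since implementation, from surveys conducted throughout the project, so 2021 could be the first half of the pair. Other national surveys are allowed as sources. Fig. 1 is not available here, and a survey calendar or an analysis role for blood pressure may sit in the full protocol.

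Much of this stands, and it rules out several stronger readings that a reader might draw:

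- **That there will be no post-intervention STEPS round, so the outcome will measure pre-intervention trend.** Later rounds are neither named nor excluded, and year 1 is undated. The conclusion is conditional on no later round occurring.
- **That glucose change has no post-intervention source at all.** The source is unspecified rather than absent.
- **That the project's blood pressure and weight data will not be used.** Nothing forbids analysing them. The article only gives them no stated outcome role.
- **That STEPS should be reduced to context.** The project surveys are small and cover only Viti Levu and Upolu, while the policies are national. Replacing one source with the other is a trade-off and does not correct an error.

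The objection does not remove the rest. The article itself fixes STEPS as the source, dates only a round near baseline, sends blood pressure and glucose change to other surveys while recording blood pressure itself, and contradicts itself on blood samples. None of these depends on detail that an article normally leaves out.

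**Conclusion.** The point holds in a limited form. As written, the health outcomes rely on an external survey with no named post-implementation round, while data that fall on either side of the interventions for blood pressure and body size have no stated role. If year 1 is 2020 or 2021, the dated round is within one year of baseline. If no later round or other suitable national survey takes place, the STEPS comparison will be largely pre-intervention.

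The project's own waves would give an estimate over the right interval, but a coarse one. With 300 per wave, a design effect of 1.5 and an assumed systolic SD of 15 to 22 mmHg, the detectable change at 0.9 power is about 5 to 7 mmHg. That supports reporting an estimate with its interval, and does not support relying on a significance test. The inconsistency on blood samples is plain and needs no assumption.

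**What to change.** 1. Add to the impact evaluation the survey-weighted change in blood pressure, BMI or overweight, and waist between the project's baseline and follow-up surveys in each country. Report it as an estimate with a 95% confidence interval, alongside STEPS.
2. State that only STEPS or other national rounds carried out after implementation count as impact evidence, and name the expected rounds and dates where known. Earlier rounds describe background trend.
3. Reconcile Strengths and limitations with Data collection process on blood samples. If blood is drawn, list it among the survey procedures and say what is measured. If not, remove the statement.
4. Keep glucose change as a main outcome only if a post-implementation source is identified, whether the project's own samples or a named external survey.

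The cost is some rewording and one further analysis of data already due to be collected. The drawbacks are limited precision, coverage of the main island only in each country, and the possibility that glucose change loses its place as a main outcome.
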